## Abstract

**Background:**

Treatment with anticoagulants, including direct oral anticoagulants (DOACs), should be considered for patients diagnosed with atrial fibrillation (AF) deemed at risk of ischaemic stroke. There are limited real world data related to the characteristics of patients with non-valvular AF who were not taking anticoagulants at the time of first ischaemic stroke and their subsequent DOAC treatment for the secondary prevention of stroke. Furthermore, little is known about patient adherence and experiences of DOAC treatment, especially for patients with non-valvular AF receiving DOAC therapy for the secondary prevention of stroke.

**Methods:**

This is a UK mixed methodology, non-interventional study, involving retrospective and prospective medical record reviews and a prospective patient survey, in progress in six UK National Health Service secondary/tertiary care centres. The study comprises two groups of patients. Group 1 will include 300 eligible consenting patients with a first ischaemic stroke associated with non-valvular AF untreated with anticoagulants in the 12 months prior to stroke. Group 2 will include a subgroup of 150 patients from Group 1 initiated on one of the DOACs targeting activated Factor X (*n* = 50 on apixaban, n = 50 on edoxaban and n = 50 on rivaroxaban). The primary endpoint of the study is the CHA_2_DS_2_-VASc Risk Score prior to initiation of anticoagulation for patients included in Group 1. Secondary endpoints to be evaluated in Group 1 include patient demographics, clinical characteristics, relevant medical history, anticoagulant therapy initiated for secondary prevention of stroke, and relevant concomitant medication. Secondary endpoints to be evaluated in Group 2 include the time between stroke and DOAC initiation; prescribing of DOACs, other anticoagulants and concomitant medication; clinical assessments and hospital resource use; patient reported outcome measures, including the Morisky Medication Adherence Scale questionnaire and the Treatment Satisfaction Questionnaire for Medication.

**Discussion:**

This mixed methodology study will provide new real world insights into the characteristics and management pathways and patient-reported experiences of this important group of patients. It is anticipated that the results of this study will provide the medical community and patients with important information to inform clinical decision-making and help facilitate meaningful improvements in the care of patients with non-valvular AF.

## Background

Atrial fibrillation (AF) is the most common chronic cardiac arrhythmia, which often remains undiagnosed and is associated with a significantly increased risk for thromboembolic stroke [1–3]. It has been estimated by the Stroke Association that approximately 20% of the more than 100,000 strokes occurring annually in the United Kingdom (UK) are associated with AF [4]. The UK National Institute for Health and Care Excellence recommends that anticoagulation is considered for patients diagnosed with AF who are deemed to be at risk of stroke, as assessed by the CHA_2_DS_2_-VASc score [5, 6].

Direct oral anticoagulants (DOACs) are a class of oral anticoagulants that have been developed and introduced to healthcare systems across the world over the past decade. The first DOAC to market, dabigatran, is a direct thrombin inhibitor which, like warfarin, has been the subject of numerous real world observational research studies [7, 8]. The three DOACs most widely used currently in the UK for the primary and secondary prevention of stroke in patients with non-valvular AF (the most common form of AF) are direct inhibitors of activated factor X (anti-FXa DOACs, namely apixaban, edoxaban and rivaroxaban) [5, 9–11]. Although some real world studies have evaluated the use and effectiveness of apixaban and rivaroxaban in patients with AF [12–14], there are limited data related to the characteristics of patients who were not taking anticoagulants at the time of first ischaemic stroke. There are also limited data related to use of anti-FXa DOACs in routine clinical practice since the introduction of edoxaban in 2015, the last DOAC to market in the UK. Furthermore, while guidance on prescribing each of the anti-FXa DOACs is available [9–11], this may not reflect how they are prescribed and taken by patients treated in routine clinical practice. Patient-related factors, including adherence, how patients perceive the benefits of treatment (including their experience and satisfaction with the treatment and overall care) may impact on treatment effectiveness. However, little is known about the extent to which patients adhere to anti-FXa DOAC treatment and their perceptions of anti-FXa DOAC treatment, especially for patients with AF receiving DOAC therapy for the secondary prevention of stroke.

### Methods/design

#### Aim and objectives

The aim of this mixed-methodology study is to evaluate the real world use of anticoagulation, in particular anti-FXa DOAC treatment (apixaban, edoxaban and rivaroxaban) in routine UK clinical practice in terms of patient characteristics, management pathways and patient-reported experiences of anticoagulation initiated following a first ischaemic stroke associated with non-valvular AF for patients who were not receiving anticoagulant therapy in the 12 months prior to the stroke.

The primary objective of this study is to describe the demographics, clinical characteristics and medical history of patients with AF presenting with a first ischaemic stroke who were not treated with anticoagulants in the 12 months prior to the stroke, according to the type of anticoagulant treatment subsequently prescribed for secondary stroke prevention (apixaban, edoxaban, rivaroxaban, warfarin, dabigatran, other anticoagulants or a documented decision not to initiate anticoagulation). Secondary study objectives will be evaluated only in patients treated with anti-FXa DOACs (apixaban, edoxaban, rivaroxaban), including describing the management pathways of patients initiated on anti-FXa DOAC treatment for secondary prevention of stroke; describing hospital resource use and the clinical assessments associated with anti-FXa DOAC treatment; describing patient-reported adherence to anti-FXa DOAC treatment; and describing patient-reported experience and satisfaction with anti-FXa DOAC treatment.

### Study design and setting

This is a UK mixed methodology, non-interventional study, involving retrospective and prospective medical record reviews and a prospective patient survey, which is in progress in six UK National Health Service (NHS) secondary and tertiary care centres. Study centres have been selected to provide good geographic representation of centres experienced in prescribing apixaban, edoxaban and rivaroxaban for the secondary prevention of ischaemic stroke in patients with non-valvular AF. The key elements of study design are summarised in Fig. 1. The index event is the diagnosis of first ischaemic stroke associated with AF. The pre-index observation period is the 12-month period prior to the index event. The post-index observation period is the one month period following the index event. The post-DOAC observation period is the period from initiation of anti-FXa DOAC treatment up to a maximum of 7 months (6 months + 1 month window for completion of questionnaires) post-initiation.

**Fig. 1 Fig1:**
[figure not shown]
Study design and observation periods. **Group 1**: retrospective data collection for 300 eligible and consenting patients who present with first stroke associated with non-valvular atrial fibrillation (index event). The pre-index observation period is the 12-month period prior to the index event. The post-index observation period is the one month period following the index event **Group 2:** Prospective data collection for the first 150 eligible and consenting patients from Group 1 who commence treatment with apixaban (*n* = 50), edoxaban (*n* = 50), or rivaroxaban (*n* = 50). The post-DOAC observation period is from initiation of anti-FXa DOAC treatment up to a maximum of 7 months (6 months + 1 month window for completion of questionnaires) post-initiation. The baseline questionnaire will be completed within one month following anti-FXa DOAC initiation. The three-month questionnaire will be completed within the period beginning one week prior to and ending one month after the three-month post-initiation time point. The six-month questionnaire will be completed within the period beginning one week prior to and ending one month after the six-month post-initiation time point

### Patients

Two groups of patients will be included in the study. Group 1 will comprise 300 patients with a first ischaemic stroke that was associated with non-valvular AF who were not treated with anticoagulants in the 12 months prior to the stroke. The primary study objective will be evaluated in Group 1. Group 2 will be a subgroup of 150 patients from Group 1, comprising 50 patients initiated on apixaban, 50 patients initiated on edoxaban and 50 patients initiated on rivaroxaban. The secondary study objectives will be evaluated in Group 2.

Patients will be eligible for inclusion in Group 1 if they are aged ≥18 years at time of presentation to the study centre with a first ischaemic stroke which, in the clinician’s opinion, is associated with non-valvular AF. Eligible patients must not have been prescribed anticoagulants for any indication in the 12 months prior to stroke diagnosis, or have a history of haemorrhagic stroke or transient ischemic attack or have a severe cognitive or emotive deficit at the time of consent. Patients will be ineligible for inclusion in Group 1 if their medical records are not available for review or if they are unwilling or unable to give written informed consent for researcher access to their medical records. Patients in Group 1 will be eligible for inclusion in Group 2 if they are initiated on apixaban, edoxaban or rivaroxaban for secondary prevention of stroke. Patients in Group 1 will be ineligible for inclusion in Group 2 if they are unwilling or unable to complete the patient-reported questionnaires.

Patients will be identified and recruited prospectively during a one-year period from the point of approval to commence recruitment at participating centres. Potentially eligible patients will be identified by members of the direct care team from local department databases. Patients fulfilling the Group 1 eligibility criteria will be approached to provide written informed consent for retrospective data collection from their medical records by members of the direct care team. Patients will be approached in consecutive chronological order, according to the date of stroke diagnosis, until the required sample size or the centre-specific recruitment target is reached. The first 50 eligible and consenting patients initiated on either apixaban, edoxaban or rivaroxaban at any of the study centres during the one year recruitment period will also be included in Group 2. Although centres included in the study will have experience of prescribing all three DOACs of interest, it is likely that some centres will favour a particular anti-FXa DOAC (although feasibility exercises suggest that the favoured DOAC will vary between centres). Recruitment of patients into Group 2 will be evaluated on an ongoing basis to monitor whether a study centre is predominately favouring one type of DOAC. To ensure there is balanced enrolment of patients into the Group 2 apixaban, edoxaban and rivaroxaban sub-groups, centre enrolment targets may be implemented to ensure balanced representation across centres in order to minimise bias.

### Data sources and data collection

#### Retrospective medical record review

Data will be collected retrospectively from the hospital medical records of patients included in Group 1 in order to describe patient demographics and clinical characteristics and relevant medical history, including the components required to assess the CHA_2_DS_2_-VASc risk score (age, sex, history of congestive heart failure, hypertension, diabetes mellitus, stroke/transient ischaemic attack/thromboembolism, vascular disease). Where relevant, primary care data will also be requested from patients’ General Practitioners (GP). Data on the type of anticoagulant treatment prescribed for secondary prevention of stroke will be collected retrospectively for the one month post-index observation period. These time periods were chosen to ensure sufficient time to capture relevant data related to patient demographic and clinical characteristics prior to first stroke, accounting for variations in appointment timing and scheduling seen in routine clinical practice. A prior scoping exercise involving five healthcare professionals suggested that the data required to evaluate the primary endpoint (summary of CHA_2_DS_2_-VASc risk characteristics) are likely to be routinely recorded. Furthermore, the CHA_2_DS_2_-VASc risk score has been shown to be a useful predictor of patient outcomes over a 12 month period [15] and so a 12 month pre-index observation period was deemed appropriate. All data obtained from medical records will be recorded in electronic case report forms (eCRFs) designed specifically for the study, using a secure web-based electronic data capture system.

### Prospective medical record review

Details of anti-FXa DOAC treatment and hospital resource utilisation will be sourced prospectively from the hospital medical records of patients included in Group 2 for the six-month period following initiation of anti-FXa DOAC treatment and entered into the eCRFs. In certain cases, it may be necessary to contact the patient’s GP to obtain information from primary care records. However, it is anticipated from feasibility assessments that important information about the patient’s treatment will be captured within the secondary care records, as it is likely that patients will be referred back into secondary care should any adjustment to their anticoagulant treatment be needed.

### Prospective patient survey

Patient-reported outcome data will be collected prospectively from patients in Group 2 via questionnaires administered at baseline (initiation of anti-FXa DOAC treatment + 1 month), and at 3 months (− 1 week/+ 1 month) and 6 months (− 1 week/+ 1 month) after initiation of anti-FXa DOAC treatment for secondary prevention of stroke. These time-points were chosen in order to allow an adequate amount of time between assessment points for DOAC treatment to take effect. Questionnaires will be administered face-to-face if patients are attending clinic at the relevant time point; they will be reminded of the study requirements and will be given the opportunity to decide whether or not they would still like to take part, prior to the questionnaire being administered. Otherwise questionnaires will be administered via telephone, which is a methodology for administration of patient questionnaires that has been used in prior studies, including a study relating to edoxaban treatment [16]. Where questionnaires are administered by telephone, the questionnaires will be posted to patients by members of their direct care team at the relevant time points to give patients an opportunity to contemplate their responses and complete the questionnaires in advance. Patients will be contacted by telephone to advise them that the questionnaire has been posted, to remind them of the study requirements and to ensure that they are still willing to participate in the study. A member of the direct care team or an external researcher will contact patients at an agreed date and time to collect their responses via telephone. The questions will be read to patients as written on the paper version and patients’ responses will be entered directly into the eCRF.

### Study endpoints and variables

The primary endpoint of the study is the CHA_2_DS_2_-VASc Risk Score (scores range from 0 to 9) prior to initiation of anticoagulation for patients included in Group 1. Secondary endpoints to be evaluated in patients in Group 1 include patient demographics (including age, sex, body mass index [BMI], smoking status, alcohol use, ethnicity) and clinical characteristics (including time from AF diagnosis until stroke, recorded stroke severity, location of presentation with stroke [e.g. Emergency Department (ED), inpatient, outpatient, GP], and key clinical and laboratory evaluations at the time of stroke (including renal function, liver function and blood parameters), relevant medical history (including history of congestive heart failure, hypertension, diabetes mellitus, vascular disease [including myocardial infarction, aortic plaque, peripheral vascular disease], renal disease, hepatic disease), anticoagulant therapy initiated for secondary prevention of stroke, and relevant concomitant medication at the time of stroke and prescribed in the one month period after stroke. Secondary endpoints to be evaluated in patients in Group 2 include: the time between index event and date of anti-FXa DOAC initiation; anti-FXa DOACs and other anticoagulants prescribed during the post-DOAC observation period (including dose, and dosing frequency and reason for choice of first DOAC treatment, changes in dose and reasons for dose changes, DOAC discontinuation, time from initiation to discontinuation of first DOAC and reason(s) for discontinuation, anticoagulant treatments subsequently prescribed and reason(s) for choice/discontinuation); relevant medications newly prescribed in the post-DOAC observation period; clinical assessments (types and results of clinical assessments); hospital resource use (number, type [outpatient, inpatient, ED, other; planned or unplanned], setting [face-to-face, telephone, other], reason for hospital visits/consultations, length of stay for inpatient admissions, time to first follow-up visit from date of DOAC initiation) during the post-DOAC observation period.

Patient reported outcome measures include the Morisky Medication Adherence Scale (MMAS-8) questionnaire [17] and the Treatment Satisfaction Questionnaire for Medication (TSQM) questionnaire [18]. The MMAS-8 is a short, eight-item measure of treatment adherence that has previously been used to assess adherence to DOAC treatment in patients with venous thromboembolism [19]. The MMAS has been used widely in different diseases, populations and countries and has been administered face-to-face or via telephone [20–22]. The MMAS-8 is quicker to complete and has a higher degree of concordance with more objective measures of treatment (such as pharmacy fill data or electronic monitoring devices) than many other self-report measures [20]. In order to gain additional insight into recent levels of treatment adherence, patients will also be asked to report whether, how and how often they had taken their current anti-FXa DOAC treatment in the past seven days using a bespoke questionnaire. The TSQM is a widely validated general measure of treatment satisfaction which has been used for a variety of treatments and disease areas, including for measuring levels of patient satisfaction with anticoagulation treatment [23], and has been administered face-to face or via telephone [22]. The bespoke questionnaire will be administered to gain an understanding of the general experiences of patients with regard to other aspects of their care, such as communication, education about anti-FXa DOAC treatment and overall hospital experience.

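### The primary CHA2DS2-VASc score is timed to anticoagulant initiation, not to the index stroke, so it is unresolved whether the index stroke's 2 points count

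*Protocol article*

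**What the plan says.** All places are in the protocol article.

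- **Study endpoints and variables** defines the single primary endpoint, for Group 1: "The primary endpoint of the study is the CHA_2_DS_2_-VASc Risk Score (scores range from 0 to 9) prior to initiation of anticoagulation". The Methods part of the abstract uses the same time anchor.
- **Study design and setting** fixes the reference event and the window before it: "The index event is the diagnosis of first ischaemic stroke associated with AF", and "The pre-index observation period is the 12-month period prior to the index event".
- **Retrospective medical record review** lists the components as age, sex and "history of congestive heart failure, hypertension, diabetes mellitus, stroke/transient ischaemic attack/thromboembolism, vascular disease". It says the periods were chosen so as to "capture relevant data related to patient demographic and clinical characteristics prior to first stroke". It then cites the score's value as a predictor over 12 months and concludes "so a 12 month pre-index observation period was deemed appropriate".
- **Patients** requires a first ischaemic stroke and rules out patients who "have a history of haemorrhagic stroke or transient ischemic attack". It does not rule out earlier thromboembolism outside the brain.
- **Aim and objectives** stratifies the primary objective by the treatment subsequently prescribed. One stratum is "or a documented decision not to initiate anticoagulation".

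**The concern.** The endpoint definition and the data-collection section point to different moments. Just before anticoagulant initiation, every Group 1 patient has already had the index stroke and could be given 2 points for it. Just before the index stroke, the stroke item is 0 for nearly everyone, because earlier ischaemic stroke, haemorrhagic stroke and TIA are all ruled out by the entry criteria. The article does not say which is meant. In addition, the stated anchor does not exist for the stratum that is never anticoagulated.

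The two scores answer different questions. One is the risk at which untreated patients had their stroke. The other is the risk present when secondary prevention is chosen. A reader of the results could not tell which was reported, and could not compare the mean with other cohorts. The section on subgroup and sensitivity analyses plans no sensitivity analysis, so nothing in the article would bring out the second version.

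**Working it through.** **1. Inputs.** The components come from Retrospective medical record review, n = 300 from Patients, and the entry criteria from Patients. Two inputs are assumptions. The item weights are not printed in the article; I take the usual ones implied by the score's name (age 0, 1 or 2; stroke/TIA/thromboembolism 0 or 2; the other five items 0 or 1). No SD for the score is given; I use 1.2 to 1.8.

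**2. The plan's own figure.** Maximum = heart failure 1 + hypertension 1 + age 2 + diabetes 1 + stroke item 2 + vascular disease 1 + sex 1 = 9; minimum = 0. The stated 0 to 9 is reproduced as the range of the instrument.

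**3. Attainable range under each reading.**

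| Reading | Stroke item | Range |
|---|---|---|
| Index stroke counted | always 2 | 2 to 9 |
| Index stroke not counted, no earlier thromboembolism | always 0 | 0 to 7 |
| Index stroke not counted, earlier non-cerebral thromboembolism scored | 0 or 2 | 0 to 9 |

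**4. Shift between readings.** A patient without earlier thromboembolism scores 0 or 2 on the item, a difference of 2. A patient with it scores 2 either way, a difference of 0. If a share p has that history, the mean shift is 2 × (1 − p):

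- p = 0: 2.0
- p = 0.05 (assumed): 1.9
- p = 0.10 (assumed): 1.8

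**5. Sampling error.** The 95% half-width is 1.96 × SD / √300.

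| Assumed SD | Half-width | 2 / half-width |
|---|---|---|
| 1.2 | 0.136 | 14.7 |
| 1.5 | 0.170 | 11.8 |
| 1.8 | 0.204 | 9.8 |

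With p = 0.10 and SD 1.8, the ratio is still 1.8 / 0.204 = 8.8.

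**6. The anchor for each stratum.** Patients started on apixaban, edoxaban, rivaroxaban, warfarin, dabigatran or another anticoagulant have an initiation date. Patients with a decision not to treat have none. Every Group 1 patient has an index stroke date.

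**The case against.** **The sections can be read together.** A score taken before the stroke is also a score taken before anticoagulation, since no Group 1 patient was prescribed an anticoagulant in the preceding 12 months. On this view the endpoint sentence gives only an outer limit, the data-collection section narrows it, and the pre-stroke score is defined for untreated patients too. This is a fair reading and may be what was intended. It has to be inferred, however. The endpoint sentence names a later event as its reference, and no sentence deals with the index stroke's points.

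**An article condenses.** Item-level scoring rules often sit in the full protocol, the eCRF guidance or the SAP, none of which is shown. That would answer a complaint about missing detail. Here the article does fix an anchor for its primary endpoint, and that anchor fits neither its own data window nor one of its own strata.

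**The study is descriptive.** Under one consistent rule, and where earlier thromboembolism is absent, the choice adds a constant 2. The SD and the differences between treatment strata do not change, and either version can be derived later. This stands. The comparison with the half-width shows how much the reported level depends on the definition; it does not measure bias in a test or lost information.

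**Three stronger readings are tempting but not supported.**

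- A reader might infer that 0 to 9 is an error. It is the instrument's range, and it is attainable before the stroke if earlier non-cerebral thromboembolism is scored, which the entry criteria allow.
- A reader might infer that the six centres will score differently and produce a mixed distribution. The article has data entered into a study-specific eCRF and pooled for analysis. Nothing says that centres compute the score.
- A reader might infer that only the pre-stroke score is valid. The primary objective is stratified by the treatment chosen afterwards, so risk at that decision is also a coherent endpoint.

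**Conclusion.** The point holds as a defect in how the primary endpoint is timed. The stated anchor comes after the index stroke, is undefined for patients who are never anticoagulated, and does not match the pre-index window justified for the same score. Whether the index stroke is scored is left open.

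The consequence is 2 points for each patient without earlier thromboembolism. The mean moves by 1.8 to 2.0 if the share with that history is between 0 and an assumed 10%. The 2-point shift is about 10 to 15 times the 95% half-width at n = 300. The ratio rests on an assumed SD of 1.2 to 1.8; the 2-point shift rests only on the usual item weights. The finding concerns the level of the primary result and what it means. It does not show that the printed range is wrong or that scoring will vary by centre.

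**What to change.** 1. Anchor the score to the index stroke date for all Group 1 patients, including those never anticoagulated.
2. Derive it centrally from the collected components by one written rule that states how the index stroke is handled.
3. Name one version as primary. The score before the stroke, with the index stroke not counted, matches the window that the article justifies. If the authors prefer risk at the secondary-prevention decision, they should say so and amend the window rationale.
4. Report the other version beside it. With the index stroke counted, the attainable range is 2 to 9.
5. Keep 0 to 9, labelled as the range of the instrument.

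The cost is a sentence in the endpoint definition, one derivation rule and one extra descriptive variable. No new data are needed, provided the eCRF records the index stroke separately from earlier stroke, TIA or thromboembolism; that should be checked first.

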### Data analysis

Statistical analyses, including any data preparation prior to analysis, will be carried out using Stata v14 (StataCorp LLC) and Microsoft Excel (2010). Data from all centres will be pooled for analysis. Study endpoints will be presented as descriptive statistics of central tendency (median; arithmetic mean or geometric mean) and dispersion (interquartile range [IQR] and/or range; standard deviation [SD] and/or 95% confidence intervals [95% CI]) and/or frequencies and percentages, as appropriate for the type and distribution of the variables.

Total scores for the validated patient-reported questionnaires will be derived in accordance with published scoring algorithms for each measure [17, 18, 25]_._ Analyses will be conducted using only the results of those patients with data available.

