### Subgroup and sensitivity analyses

All endpoints evaluated in Group 2 will be stratified according to the anti-FXa DOAC first prescribed (apixaban, edoxaban, rivaroxaban). Patient-reported outcomes will also be analysed separately for patients remaining on first anti-FXa DOAC treatment and those switching DOAC treatment during the post-DOAC observation period, in order to explore the relationship between patient-related factors and decisions to switch treatments. No sensitivity analyses are planned.

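### Time to discontinuation of the first DOAC is censored at 6 to 7 months, but the only summaries stated do not handle censoring and most naturally describe stoppers alone

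*Protocol article*

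**What the plan says.** Study endpoints and variables lists, for Group 2, "time from initiation to discontinuation of first DOAC and reason(s) for discontinuation". With the words just before it, the list runs "changes in dose and reasons for dose changes, DOAC discontinuation, time from initiation to discontinuation of first DOAC". Discontinuation and its timing are thus two separate items.

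Two limits on follow-up appear. Study design and setting says "The post-DOAC observation period is the period from initiation of anti-FXa DOAC treatment up to a maximum of 7 months", the seventh month being a window for completing questionnaires. Prospective medical record review collects treatment details "for the six-month period following initiation of anti-FXa DOAC treatment and entered into the eCRFs".

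On method, Data analysis states one rule for all endpoints: "Study endpoints will be presented as descriptive statistics of central tendency (median; arithmetic mean or geometric mean") with measures of dispersion, "and/or frequencies and percentages, as appropriate for the type and distribution of the variables". The next paragraph, after a sentence on questionnaire scoring, adds: "Analyses will be conducted using only the results of those patients with data available". Subgroup and sensitivity analyses says "All endpoints evaluated in Group 2 will be stratified according to the anti-FXa DOAC first prescribed (apixaban, edoxaban, rivaroxaban"), and plans no sensitivity analyses. The article mentions no censoring rule, Kaplan-Meier estimate or cumulative incidence.

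**The concern.** A patient still taking the first DOAC when observation ends has no discontinuation time, only a lower bound for it. A mean or median of the recorded times therefore uses only those who stopped inside the window. It cannot exceed the window length, and it gives no weight to the patients who persisted.

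At stake is the secondary objective of describing management pathways on anti-FXa DOACs. A published median of just under three months could be read as typical time on treatment when it says only when the stoppers stopped. The study is descriptive, so a misleading description is the harm itself; no comparison between drugs is needed for it to matter.

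**Working it through.** **The plan's own figure.** The article states no figure for time to discontinuation. Its only computed figure is the precision of the mean adherence score (n = 50, mean 7.2, SD 1.2), and this reproduces: 1.96 × 1.2/√50 = 0.33, giving 6.87 to 7.53, which rounds to the stated 6.9 to 7.5. It has no bearing on this endpoint.

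**Inputs.** From the article: window T = 6 months (record review) or 7 months (maximum observation), and 50 patients per DOAC. Assumed, because the article gives no stopping rate: a proportion p stopping by T of 10% to 40%, a constant hazard, and no other losses.

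**Formulas.**
- Hazard: λ = −ln(1 − p)/T
- Median time among stoppers: −ln(1 − p/2)/λ
- Mean time among stoppers: 1/λ − T(1 − p)/p
- Restricted mean time on first DOAC, all patients: (1 − e^(−λT))/λ

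Example for p = 0.20, T = 6: λ = 0.2231/6 = 0.0372 per month; median among stoppers = 0.1054/0.0372 = 2.83 months.

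| p stopping by T | Stoppers of 50 | Stoppers' median, T = 6 | Stoppers' mean, T = 6 | Restricted mean, all patients, T = 6 | Stoppers' median, T = 7 |
|---|---|---|---|---|---|
| 10% | 5 | 2.92 | 2.95 | 5.69 | 3.41 |
| 20% | 10 | 2.83 | 2.89 | 5.38 | 3.31 |
| 30% | 15 | 2.73 | 2.82 | 5.05 | 3.19 |
| 40% | 20 | 2.62 | 2.75 | 4.70 | 3.06 |

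Times are in months. Persistence falls from 90% to 60% down the table, while the stoppers-only median moves by 2.92 − 2.62 = 0.30 month. Changing the window from 6 to 7 months moves it more: 3.41 − 2.92 = 0.49 month at 10% stopping.

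**Noise by DOAC.** At 10% stopping, each DOAC contributes about 5 stoppers. Their times are roughly uniform on 0 to 6 months, so the SD is about 6/√12 = 1.73 and the standard error of their mean about 1.73/√5 = 0.77 month. The whole shift in the stoppers-only mean between 10% and 40% stopping is 2.95 − 2.75 = 0.20 month.

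**The crude percentage.** Assume in addition a 20% loss over 6 months at constant rate g = −ln(0.8)/6, and count only observed discontinuations over everyone enrolled. The expected percentage is λ/(λ + g) × (1 − e^(−6(λ + g))). For a true 20%, λ = g, giving 0.5 × (1 − 0.8 × 0.8) = 18%. For a true 40%, it is 0.696 × (1 − 0.6 × 0.8) = 36%.

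**The case against.** Four counter-arguments deserve weight.

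*Stoppers-only averaging is not written down.* The rule is generic and leaves the choice to what suits the variable, and the available-data sentence sits beside questionnaire scoring. A patient known to be on drug at 6 months could also be said to have data. This stands in part: the reading is an inference. But the latitude is among means, medians and percentages, and none of these deals with a censored time. Even without the available-data sentence, a persister has no discontinuation time to average.

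*Censoring rules belong in the SAP or full protocol, neither of which is shown.* Silence alone would be no finding. Here the article does state a general rule, and applied to this endpoint that rule gives an uninformative result.

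*Discontinuation is reported separately.* This stands and limits the point. A reader might infer that the plan could not tell a DOAC with 10% stopping from one with 40%. The documents do not support that: percentages are provided for, Group 2 endpoints are stratified by first DOAC, and the crude percentage would show the difference. Only the time statistic fails to show it.

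*The endpoint is secondary, and comparisons between DOACs are disclaimed.* This is true and bears on priority. When and why stoppers stop is a legitimate descriptive question, provided the answer is labelled as conditional on stopping.

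Two further inferences should also be resisted. One is to set the stoppers' median against a true median time on drug. For 10% to 40% stopping, that true median would lie beyond the 7-month maximum, could be reached only by extrapolating an assumed hazard, and could not be estimated by any method from this follow-up. The other is to extend the criticism to time to first follow-up visit. Nothing in the article indicates how many patients would lack a visit in the window.

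**Conclusion.** The concern holds for this one endpoint. Time to discontinuation of the first DOAC is right-censored at 6 to 7 months, and the summaries stated for it ignore that. On the natural reading, the reported median would be about 2.6 to 2.9 months (3.1 to 3.4 with a 7-month window) whether 10% or 40% of patients stop, so it says little about persistence. The separate percentage partly compensates, but it carries no timing and understates discontinuation if patients are lost early: 18% for a true 20% and 36% for a true 40%, under an assumed 20% loss.

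The sizes rest on a constant hazard and on assumed stopping and loss rates. A different hazard shape would move the stoppers' median within the window, but that median would still exclude everyone who persisted. The change is worth making because it is nearly free; it does not touch the primary endpoint.

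**What to change.** - State that patients still on the first DOAC are censored at withdrawal or end of observation.
- Reconcile the 6-month record review with the 7-month maximum observation period, so that one end date applies to this endpoint.
- Report the cumulative incidence of first-DOAC discontinuation at 3 and 6 months with 95% CI, overall and by first DOAC, using Kaplan-Meier, or Aalen-Johansen with death as a competing event.
- Keep the reasons for discontinuation as frequencies.
- If a mean or median among stoppers is still shown, label it as conditional on stopping and give its denominator.

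The cost is a few lines of analysis text and a minor extra analysis. The endpoint already implies dates of initiation and discontinuation; dates of last observation and of death must also be recorded. Precision by DOAC will be modest: at 20% stopping with 50 patients and no losses, the 95% half-width is about 1.96 × √(0.2 × 0.8/50) = 0.11, or 11 percentage points. The interval should therefore be printed with each estimate.
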